# Clinical efficacy of ceramic versus resin-based composite endocrowns in Chinese adults: study protocol for a randomized controlled trial

**DOI:** 10.1186/s13063-020-04506-9

**Published:** 2020-06-22

**Keywords:** Endocrown, CAD/CAM, Ceramic, Resin composite, Endodontically treated teeth, Randomized controlled trial

## Abstract

**Background:**

Endocrown restoration is widely used to restore endodontically treated teeth. However, the clinical effects of different computer-aided design/computer-aided manufacturing (CAD/CAM) materials for endocrown restoration are not clear. The primary objective of this trial is to compare the clinical efficacy of resin-based bloc and ceramic endocrowns for restoring endodontically treated teeth.

**Methods:**

The proposed resin-based bloc and ceramic endocrown assessment trial is a parallel group-designed randomized controlled trial. We will recruit 156 adults between 18 and 75 years old with a minimum of one such molar. The inclusion criteria were good oral hygiene habits, root apex of molar without evident damage, receipt of standard endodontic treatment, need for endocrown restoration, and only one endocrown restoration performed per patient. Patients participating in another study or those with systemic diseases, disabilities, or known allergies to used materials will be excluded. All patients will be randomized and restored with resin-based bloc and ceramic endocrown according to a random number table. Clinical evaluations will be performed at baseline and after treatment at 6, 12, and 24 months, in accordance with the modified Federation Dentaire Internationale (FDI) criteria, by two independent evaluators. The primary outcome is marginal adaptation; secondary outcomes include wear, tooth integrity, fracture of material and retention, marginal staining, and patient view. All data will be analyzed by an independent statistician. Signed rank-sum tests will be used for intragroup comparisons. Wilcoxon rank-sum tests will be used for intergroup comparisons. Hierarchical logistic regression will be used to adjust the baseline and other important indicators.

**Discussion:**

This study will investigate endocrowns of two CAD/CAM materials for endodontically treated molars. The results may help clinicians choose the better CAD/CAM material option and explain to patients the advantages and disadvantages of these two materials with evidence-based support. For patients, the results may lead to improvement in long-term restoration.

**Trial registration:**

ClinicalTrials.gov NCT04033380. Registered on 24 July 2019

## Background

Pulp disease and periapical disease are common oral diseases, and root canal therapy (RCT) is the most effective and ultimate treatment for these diseases [1]. In clinical practice, it is a major challenge to repair the tooth after RCT, since they will be more fragile than vital teeth [2]. If the restoration is not well done in time, the prognosis will decrease greatly, and tooth fracture is one of the most essential causes of treatment failure [3]. After the RCT, excessive removal of surrounding dentin tissue and pulps will cause damage to the overall structure of the tooth, the strength of the tooth will be reduced, and the tooth will lose the nutritional support of the pulp, eventually leading to tooth fracture [4]. Therefore, the endodontically treated teeth should be repaired in time [5]. Endocrowns, full crowns, and post-core crowns are often used to repair these teeth [6]. However, the full crown needs to cut a mass of dental tissues, which results in a significant reduction in the remaining healthy dental tissues [7]. Although post-core crown restoration can strengthen residual dental hard tissue and replace missing dental tissue, which provides the retaining force for the crown, post-core crown restoration can result in additional risks, such as canal perforation and root fracture [8]. Along with the increasing emphasis on minimally invasive trends and the development of adhesive dentistry, an increasing number of clinicians prefer to choose ways to retain more healthy dental tissues [9].

In recent years, the endocrown has been recognized as a new restoration method along with the advantage of minimally invasive treatment [10]. Endocrown is a kind of onlay that is composed of a butt plane and retainer deeply fixed into the internal walls of the pulp chamber [11]. Endocrowns are one-piece constructs that integrate the post, core, and crown to form a complete block prosthesis. In contrast to traditional internal fixation methods, endocrowns are anchored in the inner and margin of the pulp cavity, and the retentive effect better benefits from the macroscopic and microscopic mechanical retentions provided by the pulp cavity and adhesion [12]. Compared with full crown restoration, the endocrown loses less hard tissue, requires less clinical chair time, and the masticatory stress dispersion at the tooth/prosthesis interface is more scientific [13]. Compared with post-core crown techniques, endocrown restoration is simplified because of the core-crown integrity. Furthermore, no post is needed, reducing the risk of root fracture [11]. In a systematic review of three clinical trials, endocrown restorations achieved 94–100% success, which was superior to that of traditional full crown restorations in the anterior teeth [14]. Endocrowns were also shown to restore severely damaged molars. The survival rate was excellent at 99.0% after 44.7 ± 34.6 months, which was superior to that documented in existing data on post- and core-based single crowns [15, 16].

The indications of endocrown include extensive dental defects, inadequate intermaxillary space, lack of the thickness requirements of ceramic materials, inability to use post-core crown or crown for restoration, and cases in which full crown restoration is prohibited due to anatomic variation of the posterior root [17]. We are currently processing a clinical trial on the effect of two marginal endocrown designs, and we found that the flat marginal design was easier to prepare than the 90° shoulder endocrown was [18]. Therefore, the flat marginal form was used in this study (Fig. 1). At present, the fabrication of endocrowns is usually completed by chairside CAD/CAM [19]. CAD/CAM technology has the advantages of high efficiency and accuracy, significantly shortens the production time of restorations [20], and enables clinicians to provide high-quality esthetic restorations in a chairside manner. With the development of CAD/CAM systems, various CAD/CAM materials have been introduced [21]. It has been reported that the restorative effect of endocrowns is closely related to CAD/CAM materials [22]. Leucite-reinforced lithium disilicate and zirconia-reinforced lithium silicate ceramics are thought to be the best choice with the advantages of esthetic and mechanical properties, translucency to natural teeth, good biocompatibility, anti-corrosion, anti-aging, and anti-abrasion [22, 23]. However, ceramic materials have high brittleness, and porcelain fracture frequently occurs and leads to restoration failure [24, 25]. Most ceramic restorations with chairside CAD/CAM require a second sintering. Studies have shown that the crystallization firing process results in a significant increase in the marginal gap size, likely due to shrinkage of the ceramic during the crystallization process [26, 27]. The gap between the tooth and endocrown will reduce the compatibility between the restoration and the tooth and lead to the failure of the restoration.

**Fig. 1 Fig1:**
[figure not shown]
Schematic representation of the flat endocrown

More recently, ongoing research on biocompatible materials with physical and mechanical properties similar to those of natural tooth tissues has introduced a new generation of nanohybrid composite restorative materials (Grandio blocs, VOCO GmbH, Cuxhaven, Germany). The compositions of resin nanofillers allow the material to have a modulus of elasticity (18.0 GPa) similar to that of dentin. The advantages of resin-based restorations are showing less crack propagation and providing better flexural strength than some CAD/CAM ceramics are [28, 29]. Moreover, resin-based composites are easily cut, cause little damage to grinding burs, and are convenient for repair in the mouth when defects occur.

Because there are no sufficient clinical data to verify that endocrowns fabricated from different CAD/CAM materials are more suitable for the restoration of endodontically treated molars, the main aim of this trial was to compare the clinical efficacy of ceramic versus resin-based bloc endocrowns and to predict the clinical outcomes of these two restorations used for endodontically treated teeth.

### Objective

The main objective is to compare the clinical efficacy of resin-based bloc and ceramic endocrowns in treating endodontically treated molars by assessing the marginal adaptation of restorations fabricated with a chairside CAD/CAM system (Dentsply Sirona, Bensheim, Germany). The minor objectives include evaluating the wear, radiographic examination, patient’s view, and recurrence of caries between the study groups during the same period and looking for the prognostic and influencing factors of the related effects.

### Hypothesis

Our working hypothesis is that the restorative effect of the resin-based bloc endocrown is superior to that of the ceramic endocrown.

## Methods

### Trial design and blindness

This is a randomization, parallel control, optimal design trial with two balanced parallel arms (see SPIRIT checklist, Additional file 1). A double-blinding strategy was designed in this trial. The patients and data analysts are blinded. Operators cannot be blinded because the surface treatment method of ceramic and resin endocrowns is different (in particular, the treatment of the intaglio surfaces of the restoration). It is not possible to blind evaluators because a dentist can easily recognize the material type.

### Block randomization

The method of block randomization is adopted, the block length is set as 6, the number of random seeds is set as “20190811,” and software SAS9.4 was used. All patients who gave consent for participation and who fulfilled the inclusion criteria were randomized. Randomization will be requested by the staff member from the Centre of Clinical Trials (Cen-Trial). After root canal treatment, the allocation of patients will be implemented according to the indication in the random number table. A nurse will call Cen-Trial and tell the doctors about the intervention, and then she will only write the treatment number in the patient’s CRF file. Randomization will be conducted without any influence of the principal investigators, rates, or therapists.

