### Sample size and recruitment procedures

The main evaluation index was the marginal adaptation of the restoration. In this study, the proportions of grades A (clinically excellent), B (clinically good), C (borderline quality/acceptance, repair necessary/possible), and D (clinically unsatisfactory, replacement necessary) in the experimental group are expected to be 60%, 30%, 8%, and 2%, respectively. The proportions of grades A, B, C, and D in the control group are expected to be 40%, 30%, 20%, and 10%, respectively. After a bilateral inspection level of 0.05 was set and the power of the test was set to no lower than 80%, nQuery 8.0 software was applied to calculate the sample size, in which 124 patients (62 for each group) were recruited. Considering that 20% of patients might drop out in the follow-up, the final recruitment sample size of this trial would be 156 patients (78 in each group).

The participants will be recruited from the Department of Conservative and Endodontic Dentistry in Nanfang Hospital, Southern Medical University. There are many patients with root canal treatment in this department each year. Approximately 20–30 endocrown restorations have been fabricated by CAD/CAM in this hospital each month according to the data of last year. Therefore, the achievement of adequate participants is feasible in 2 years. We promise compensation to the patients who participate in the study. Every half a year, all the participants will receive free dental care including teeth cleaning and X-ray examination and oral examination. Every 3 months, a phone call follow-up will be executed to evaluate participants’ general condition. The traffic fee for each visit will be compensated.

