### The intervention group and control group

All participants will be randomly allocated into two groups. One group will receive a Vita suprinity endocrown, and the other group will receive with Grandio bloc endocrown (Table 2). Randomization will be performed in accordance with a random list of numbers generated by the Department of Biomedical Statistics of Southern Medical University. The 5 operators are endodontists from the Department of Conservative and Endodontic Dentistry in Nanfang Hospital, Southern Medical University, and all of them will be eligible for inclusion and will receive standardized training in endocrown restoration as previously described before the study begins [18]. The chairside CAD/CAM endocrown will be designed and fabricated by the same technician. The number of cases assigned to each dentist is approximately 30. Another two dentists will serve as evaluators and will be responsible for observing the restorations and collecting data during follow-up.

**Table 2 Tab2:** SPIRIT (Standard Protocol Items: Recommendations for Interventional Trials)

TIMEPOINT	Pre-treatment	Post-treatment	6-month follow-up	12-month follow-up	24-month follow-up

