### Trial status

The protocol version number is NFEC-2017-141 and approved on Sep. 7, 2017. This trial is in the process of recruiting participants. The trial recruiting has started on Jul. 26, 2019, and the recruitment will be completed in 2 years.

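### The fixed block length, seed and software of the randomisation list were published while recruitment was open, so the remaining allocations could be worked out on site

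*Protocol article*

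**What the plan says.** In the protocol article, the section Block randomization states that "the block length is set as 6, the number of random seeds is set as “20190811,” and software SAS9.4 was used". Trial design and blindness adds an "optimal design trial with two balanced parallel arms", so each block holds 3 and 3. No other block length is mentioned.

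On timing, the article carries the publication date 22 June 2020. Trial status says "This trial is in the process of recruiting participants" and "The trial recruiting has started on Jul. 26, 2019, and the recruitment will be completed in 2 years". Sample size and recruitment procedures gives the target: "the final recruitment sample size of this trial would be 156 patients (78 in each group").

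On who learns the allocations, Trial design and blindness says "Operators cannot be blinded because the surface treatment method of ceramic and resin endocrowns is different", and of the assessors, "It is not possible to blind evaluators because a dentist can easily recognize the material type". The section on the intervention and control groups says "The 5 operators are endodontists from the Department of Conservative and Endodontic Dentistry in Nanfang Hospital", with about 30 cases each, and that the same technician designs and fabricates the endocrowns. Under Block randomization, a nurse telephones Cen-Trial and passes the allocation to the doctors. The same section states that randomisation takes place without influence from investigators or therapists.

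**The concern.** Central telephone allocation protects a trial only while the list cannot be derived by people on site. Here the article prints the main ingredients of the list during recruitment, and staff on site already hold a growing record of true allocations against which to test a reconstruction. Separately, one fixed block length in a single department with open treatment makes the end of each block predictable to anyone who follows the whole sequence.

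Someone who knows the next material could influence which patient takes that place. The possible routes are the timing of entry and the exclusion criterion that leaves suitability to the researchers' judgement. There is room for this: 20 to 30 endocrowns a month is 480 to 720 over 24 months, for 156 places. The evaluators are unblinded as well, so later masking gives no protection. The planned regression can adjust for measured baseline differences but would not remove selection on unmeasured ones.

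**Working it through.** **Plan figures reproduced.** Two arms of 78 give 156, and 156 / 6 = 26 complete blocks, so the block length fits the target. The inflation for dropout also holds: 62 / (1 − 0.20) = 77.5, rounded up to 78 per group. The sample size is not affected by this point.

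**1. How many patients were still to be randomised at publication.** Inputs: start 26 July 2019 and planned length 2 years (Trial status), publication 22 June 2020, target 156. The number already randomised is not stated, so even accrual is assumed.
- Elapsed: 332 of 731 days = 45.4%.
- Randomised: 0.454 × 156 = 71. Remaining: 156 − 71 = 85 (55%), about 14 blocks.
- Accrual 25% faster: 156 − 1.25 × 70.85 = 67 remaining (43%).
- Accrual 25% slower: 156 − 0.75 × 70.85 = 103 remaining (66%).

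**2. If the list is rebuilt from the seed.** The article gives block length, seed, program and allocation ratio. It does not give the SAS procedure, the code or the arm coding, so several candidate programs would have to be tried. A 3:3 block has 6! / (3! × 3!) = 20 possible orders. If these are equally likely, a wrong candidate list matches one known block with probability 1/20, and three known blocks with probability (1/20)³ = 1/8,000. With about 71 patients randomised, about 11 complete blocks would be available for checking. A correct reconstruction could therefore be recognised, and all remaining allocations would then be known.

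**3. Without the seed, for someone who sees every earlier allocation.** Over the 20 equally likely orders, by position in the block:

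| Position | Known with certainty | Best guess correct |
|---|---|---|
| 1 | 0 | 0.5 |
| 2 | 0 | 0.6 |
| 3 | 0 | 0.6 |
| 4 | 0.1 | 0.7 |
| 5 | 0.4 | 0.7 |
| 6 | 1.0 | 1.0 |
| Sum | 1.5 | 4.1 |

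That is 1.5 / 6 = 25% certain and 4.1 / 6 = 68% guessed correctly, against 50% by chance. For 85 remaining patients it means about 21 certain and 58 correct guesses, against about 43 by chance.

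**4. Without the seed, for one operator alone.** Five operators with about 30 cases each see about one allocation in five. The same enumeration, with each earlier allocation seen with probability 0.2 and the position in the block granted, gives 54.0% correct guesses and 0.2% certain allocations.

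**The case against.** A reader might infer that the article contains everything needed to regenerate the list, so that the operators know what is coming. The documents do not support that. The procedure, code and arm coding are missing, and rebuilding the list would be a deliberate act of subversion. Nothing shows that anyone attempted it.

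A reader might also apply the 25% and 68% to each operator. Step 4 shows that this is wrong: those figures need knowledge of the full sequence. The technician who makes all the endocrowns, the nurse who makes the calls, or operators who pool their records could have it.

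Third, no section says that operators screen, consent or enrol. Randomisation is requested by Cen-Trial staff for consenting, eligible patients, the list comes from the university's statistics department, and investigator influence is ruled out. Operators steering entry is therefore an inference. It is a plausible one, with one department and a discretionary exclusion.

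Fourth, the count of 85 depends on accrual. At 20 to 30 endocrowns a month, about 220 to 330 were made in the 11 months before publication, so with high uptake recruitment could have run well ahead of even accrual.

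All four limits stand. They make the point conditional but do not remove it, because the telephone call and the statement of independence protect only a list that cannot be derived.

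**Conclusion.** The point holds as a conditional weakness in allocation concealment. A single fixed block length, the exact seed and the program were made public during recruitment to a trial with unblinded operators and evaluators. If the list is rebuilt, all remaining allocations are known: about 85 of 156 under even accrual, or 67 to 103 with accrual 25% faster or slower. Without the seed, 25% are certain and 68% guessable to someone who sees the whole sequence, and 0.2% and 54% to an operator who sees only a fifth of it.

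The documents show that concealment could be broken. They do not show that it was, and they do not establish a bias in the result. The conclusion assumes that the published seed and block length are those of the list in use, and that the list was not replaced; the article does not say that it was.

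**What to change.** - From the next unused block, have the Department of Biomedical Statistics replace the rest of the list. Use an undisclosed seed and undisclosed, randomly varying block sizes, chosen so that the total stays 78:78.
- Hold the new list only at Cen-Trial, and disclose none of its parameters until recruitment closes. What is already published cannot be withdrawn, so only replacing the list helps. The new seed can be archived and released afterwards for reproducibility.
- Document the date of the change and the last patient allocated from the old list.
- Compare baseline balance between arms for patients randomised before and after publication. Present this as descriptive: two parts of roughly 71 and 85 patients, before 20% dropout, have little power to show a problem, and a reassuring result would not prove concealment.
- If recruitment has closed, report that comparison and state the concealment limitation in the results paper.

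The cost is a few hours of a statistician's time and a short amendment. The drawback is a documented change of list in mid-trial. The target sample size does not change.

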### Participants

The participants will be recruited from the Department of Conservative and Endodontic Dentistry in Nanfang Hospital, Southern Medical University. No special concomitant dental care or intervention is prohibited in participants after inclusion in the trial, except that concerning the included teeth.

### Inclusion criteria

The patients are adults aged around 18–75 years and have root apex of molar without evident damage and no root fracture.Good oral hygiene habits.Have a complete root canal therapy molar necessitating an endocrown restoration.The patient has signed an informed consent form.Only one endocrown restoration per patient is eligible.

### Exclusion criteria

Allergy to one of the materials used.Poor oral hygiene, bruxism.Severe periodontitis.Pregnancy.Incapable of self-care, mental illness or systemic diseases, and undergoing radiotherapy.Unsuitable for the trial as deemed by the researchers.

### Eligibility criteria

The dentist who works in the Division of Endodontics, Department of Stomatology, Nanfang Hospital, Southern Medical University, will perform the interventions.The dentist who will perform the intervention must be licensed as a dentist and had an experience of CAD/CAM technique for at least 3 years.

### Dropout criteria

Voluntary withdrawal from the trial by the patient.Poor clinical compliance.

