### Outcome measures

Clinical evaluations will be conducted at baseline and after 6, 12, and 24 months of follow-up according to Federation Dentaire International (FDI) criteria by two independent evaluators (Table 1) [30–32]. A standardized training program must be finished by the two evaluators before the trial begins. The two evaluators were trained in the use of the criteria at Nanfang Hospital, SMU. During the first session, the rationale for the FDI criteria, the rating system, the coding system, and the record forms were explained and discussed. Ten restorations were then rated by the instructor to clinically illustrate the rating system. After the instructor explained the reason for assigning each rating, the trainees examined the same restorations. Each trainee was encouraged to explain his or her interpretation of each characteristic and thus his or her reasons for agreement or disagreement with ratings assigned by the instructor. Where disagreements occurred, the categories were again explained so that all examiners would invoke the same concepts when using the rating scales. If the two evaluators present inconsistent evaluations, a third evaluator will perform an evaluation, and the concurring evaluations from the evaluators will be used for analysis. The primary outcome, the marginal adaption of the restoration, will be measured based on the FDI criteria. When a case is evaluated with all items at level A, the restoration is considered a success. When a case has one item at level B and the other at a level no lower than level B, the restoration is considered acceptable, requiring further observation. If a case has any item at level C or D, it is considered a failure. Secondary outcomes which include wear, proximal anatomical form, radiographic examination, patient’s view, recurrence of caries, erosion, abfraction, tooth integrity, periodontal response, adjacent mucosa, oral and general health, surface luster, staining, color match and translucency, esthetic anatomical form, and fracture of material and retention will also be analyzed with FDI criteria.

**Table 1 Tab1:** Modified FDI criteria

Category	Sub-categories	Grading
**a) Functional properties**	1. Marginal adaptation	A. Clinically excellent B. Clinically good C. Borderline quality/acceptance, repair necessary/possible D. Clinically unsatisfactory (replacement necessary)
	2. Wear	
	3. Proximal anatomical form (contact point/food impact)	
	4. Radiographic examination	

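### Poor compliance is a ground for dropout apart from the patient's own withdrawal; with operators and evaluators unblinded, it could end follow-up selectively and bias the marginal-adaptation comparison

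*Protocol article*

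**What the plan says.** The Dropout criteria section of the protocol article contains two items and nothing else: "Voluntary withdrawal from the trial by the patient.Poor clinical compliance". The second, "Poor clinical compliance", is separate from the patient's own decision. It has no definition, threshold or timing, and the article does not say who applies it.

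The section on trial design and blinding says "The patients and data analysts are blinded". It also says "Operators cannot be blinded because the surface treatment method of ceramic and resin endocrowns is different" and "It is not possible to blind evaluators because a dentist can easily recognize the material type".

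The section on the intervention and control groups gives the evaluators a double role: "Another two dentists will serve as evaluators and will be responsible for observing the restorations and collecting data during follow-up". Under Outcome measures, "Clinical evaluations will be conducted at baseline and after 6, 12, and 24 months of follow-up".

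The sample-size section inflates the target: "Considering that 20% of patients might drop out in the follow-up", so 62 evaluable patients per group become 78 recruited per group.

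**The concern.** The intervention is a single restoration, and the article describes no continuing study treatment that a patient could fail to take. Poor compliance is therefore most naturally read as poor attendance or poor oral hygiene. Hygiene can plausibly affect several graded items (recurrent caries, periodontal response, marginal staining), and attendance can go with satisfaction. Good hygiene is already required at entry, so the criterion is not needed to protect eligibility.

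Because the criterion stands apart from voluntary withdrawal, someone other than the patient would apply it. Of the roles that the article names in its blinding section, only patients and data analysts are blinded. By the 12- and 24-month visits the evaluators have already graded the same restorations. The article also declares a working hypothesis that resin is superior, so an unconscious leaning could have a direction.

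What is at stake is the comparability created by randomisation. If follow-up ends more readily for poorly graded patients in one arm, the grades observed later in that arm look better than they should. An intention-to-treat analysis set defined elsewhere could keep such a patient in the denominator, but it could not restore a 12- or 24-month grade that was never taken. The remedy therefore belongs in the conduct of follow-up.

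**Working it through.** **1. The plan's own figure.** Inputs from the sample-size section: experimental grades A to D 60/30/8/2%, control 40/30/20/10%, two-sided 0.05, power at least 80%, 20% dropout.

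Probability that an experimental patient has the better grade, counting ties as half:
0.60 × (0.60 + 0.20) + 0.30 × (0.30 + 0.15) + 0.08 × (0.10 + 0.10) + 0.02 × 0.05 = 0.480 + 0.135 + 0.016 + 0.001 = 0.632.

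Average distribution of the two arms: 50/30/14/6%. Tie factor: 1 − (0.50³ + 0.30³ + 0.14³ + 0.06³) = 0.845.

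Standard deviation term under the null: √(2 × 0.845/12) = 0.375. The corresponding term under the alternative, from the two grade distributions, is 0.359.

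n per group = [(1.96 × 0.375 + 0.842 × 0.359)/(0.632 − 0.5)]² = 61.8, so 62. Simulated power at 62 per group is 80.2%. Dropout: 62/0.80 = 77.5, so 78. The plan's 62 and 78 reproduce; the sample size is not in error.

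**2. Room for removals.** The dropout allowance is 0.20 × 78 = 15.6 patients per arm. At 50/30/14/6%, the expected number of grade C or D patients per arm is also 78 × (0.14 + 0.06) = 15.6.

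**3. Type I error when removal depends on grade.** Common assumptions: no true difference, 78 per arm, tie-corrected Wilcoxon rank-sum test, two-sided 0.05. How many patients are removed, and from which arm, is assumed; the article gives no figure.

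(a) *Not selective, or equal in both arms.* With both arms at the control distribution, removing 20% of each arm regardless of grade gives 4.7%; removing half of the C/D patients in both arms gives 4.9%. Rerun with both arms at 50/30/14/6%, these are 5.0% and 4.9%. There is no inflation.

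(b) *A fraction of C/D patients removed at random, one arm only* (10,000 runs):

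| Share of C/D removed | Expected number removed at 50/30/14/6% | Error at 50/30/14/6% | Error with both arms at 40/30/20/10% |
|---|---|---|---|
| 0% | 0 | 4.9% | 4.9% |
| 10% | 1.6 | 5.5% | 5.4% |
| 25% | 3.9 | 7.7% | 10.2% |
| 50% | 7.8 | 17.1% | 27.5% |
| 75% | 11.7 | 37.4% | 60.3% |

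The simulation standard error near 17% is √(0.17 × 0.83/10,000) = 0.4 percentage points.

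(c) *Extreme: k patients removed from one arm, all D first and then C*, at 50/30/14/6% (200,000 runs): k = 4 gives 9.8%, k = 8 gives 21.9%, k = 12 gives 40.0%. As shares of the expected 15.6 C/D patients, these are 4/15.6 = 26%, 8/15.6 = 51% and 12/15.6 = 77%.

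**4. Power under equal, outcome-related removal.** With the planned effect and half of the C/D patients removed in both arms, power falls from 88.5% (78 per arm, none removed) to 63.5%. Expected removals are 78 × 0.10 × 0.5 = 3.9 experimental and 78 × 0.30 × 0.5 = 11.7 control, together 15.6 of 156, or 10%. That is within the 20% allowance, which protects power only against loss unrelated to outcome.

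**The case against.** The strongest reply is that a short line is being made to carry a great deal. Four stronger readings are tempting, and the article does not support them.

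- *That unblinded staff remove patients after seeing their results.* The article does not say who applies the criterion or when. That unblinded staff would do so is an inference from the list of blinded roles.
- *That compliance can only mean hygiene or attendance.* The Participants section restricts dental care concerning the included tooth, so outside treatment of that tooth is another possible breach. The schedule table puts randomisation before treatment, so a patient might also fail to return for placement, before any grade exists.
- *That removed patients disappear from the comparison.* The article says neither that dropouts are excluded from analysis nor that their earlier grades are discarded. Analysis sets and the handling of missing data may be set out in documents not shown.
- *That the error rate would be 22% or 40%.* Those figures need about half or three quarters of one arm's expected C/D patients to be removed, worst first, with none removed from the other arm.

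On the attendance reading, moreover, a patient who misses a visit has no grade there to act on, and the line may merely label ordinary loss to follow-up. Deleting it would then change little.

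All of this limits the claim. What stands is that the criterion is written separately from withdrawal, that it is open-ended, and that applying it ends follow-up after randomisation for reasons that can relate to outcome, in a trial whose evaluators know both material and earlier grades.

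**Conclusion.** The concern holds as a conditional risk: the criterion could bias the comparison; nothing shows that it does. It rests on two assumptions, that someone who knows the material and earlier grades applies the criterion, and that removal relates to grade differently in the two arms. If either fails, the inflation calculated here does not arise, and the type I error stays near 5%.

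If both hold, the plausible range at 50/30/14/6% runs from almost no inflation (about 5%) to about 17%, as the share of one arm's C/D patients removed goes from 10% to 50%. The 10%, 22% and 40% figures mark the extreme and are not expectations. With both arms at the control distribution, the same 10% to 50% shares give 5.4% to 27.5%. Removals of this size fit within the planned 20% dropout and need not stand out. The sample-size calculation is unaffected.

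**What to change.** Delete poor clinical compliance from the Dropout criteria section. State instead that only withdrawal of consent or loss to follow-up ends follow-up. Patients with poor compliance stay in the trial, are recalled at every scheduled visit (6, 12 and 24 months), keep all grades already recorded, and are analysed in the arm to which they were randomised. All visits are named because the article does not single one out for the primary outcome. Record compliance as a descriptive variable.

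This costs one deleted line, a sentence or two of new text, and a little extra recall effort. The three-monthly telephone calls, half-yearly free dental care and travel compensation described in the recruitment section already support that effort.
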